### Treatment protocol and follow-up procedures

The frequency of visits will be determined by the individual study sites, and the data will be gathered as part of standard local routine. Only data collection at 1 month and at 1 year follow-up will be performed separately for the purpose of the study.

Data will be collected at various time points, including baseline (occurring as soon as the woman has discovered her pregnancy through a positive pregnancy test), standard routine visits throughout pregnancy, delivery (relating both to the mother and the neonate), 1-month follow-up and end of study (1-year follow-up) (Fig. 1). Postpartum follow-up at 1 month and 1 year will be performed using questionnaires (see Additional files 1 and 2) and telephone interviews. The 1-month follow-up will collect information on height, weight, neonatal death (yes or no), congenital malformations not detected at delivery, duration of exclusive/partial lactation and any adverse events (AEs) relating to the neonate. The 1-year follow-up will collect information on the duration of exclusive and any lactation, height, weight, diabetes in the infant (yes or no), changes in major congenital malformations and any AEs relating to the infant.

**Fig. 1 Fig1:**
[figure not shown]
Study roadmap for each subject

### Statistical considerations

The analysis set will consist of all pregnancies among patients who are treated with basal insulin and have not changed basal insulin product for 4 weeks prior to conception and during pregnancy. Continuous variables will be summarised with descriptive statistics, and categorical variables will be displayed in frequency tables.

The primary endpoint will be analysed using a logistic regression model that will include treatment group, study site, race, hypertension, major hypoglycaemic events during pregnancy, folic acid intake and use of GLP-1 agonists during pregnancy as factors. HbA_1c_ at the start of pregnancy, the end of the first trimester and the end of the second trimester, age and body mass index at baseline, duration of diabetes, blood pressure and previous perinatal complications will be included as covariates. The primary endpoint will be computed for the IDet group and for the ‘other basal insulin’ group and the absolute difference between these proportions calculated, along with the 95% CI and the *p*-value using Fisher’s exact test.

For infant endpoints at 1 year, the proportions will also be analysed using logistic regression. Factors and covariates will be as per the primary endpoint. Analyses regarding height and weight will also be adjusted for exclusive and/or partial lactation period. Similar analyses will be performed for all other endpoints that are proportions.

Means of the continuous endpoints will be compared between the two groups using an analysis of covariance model.

The incidence of major hypoglycaemia during pregnancy will be computed for both treatment groups.

Observations of possible clinical importance (such as the primary endpoint split out according to diabetes type, insulin analogue or use of an insulin pump) will be presented using descriptive statistics.

All statistical analyses will be performed using appropriate statistical software, and tests will be performed as two-sided tests with a significance level of 0.05.

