Major hypoglycaemia	A hypoglycaemic episode in which the patient is not able to treat themselves and in which oral carbohydrates, glucagon or intravenous glucose has to be administered to the patient by another person because of severe central nervous system dysfunction
Neonatal death	Death of an infant between 7 and 28 completed days after delivery
Perinatal death	Death of a foetus/infant at ≥22 completed gestational weeks and <1 completed week after delivery
Preterm delivery	Delivery before 37 completed gestational weeks
Pre-eclampsia	A condition in pregnancy characterised by new onset of abrupt hypertension (≥140/90 mmHg documented on two occasions, ≥6 h and ≤7 days apart) and proteinuria/albuminuria
Spontaneous abortion	A naturally occurring termination of a pregnancy before 22 completed gestation weeks

The study has a fixed recruitment period of 5 years (September 2013 to September 2018), and will include gestation and follow-up of infants at 1 month and 1 year of age. The planned enrolment is 3055 patients.

The study population will include women with T1D or T2D (as assessed from maternal medical history) who are pregnant and being treated with insulin or other injectable antidiabetic treatment regimens, and who have not changed their basal insulin or other injectable antidiabetic treatment for 4 weeks prior to and following conception. Inclusion and exclusion criteria are listed in Table 2.

**Table 2 Tab2:** Inclusion and exclusion criteria

Inclusion criteria
• Woman with a positive pregnancy test
• Type 1 diabetes or type 2 diabetes, diagnosed prior to conception
• Treated with unchanged basal insulin or other injectable antidiabetic treatment (for those not treated with basal insulin) for 4 weeks prior to and following conception
• Informed consent obtained before any data collection
Exclusion criteria
• Women who have been pregnant for >12 weeks at baseline visit confirmed by ultrasound

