### Study endpoints

The primary endpoint is the proportion of pregnancies in women treated with IDet, compared with other basal insulin regimens, which do not result in any of the following events: major congenital malformations, perinatal death or neonatal death (assessed at up to 4 weeks after delivery).

Key secondary endpoints relate to outcomes with IDet versus other basal insulin regimens for the mother, the fetus and the infant at 1 year of age. Maternal endpoints include the incidence of major hypoglycaemia during pregnancy, the proportion of pregnancies complicated by pre-eclampsia and metabolic control (measured as HbA_1c_). Perinatal outcome endpoints include the proportion resulting in fetal macrosomia, LGA, preterm delivery or spontaneous abortion. Infant endpoints assessed at 1 year of age include height, weight, the proportion with diabetes, and the proportion with changes (progression/regression) of major congenital malformations.

Safety data will also be collected in the pregnant women participating in the study, as well as in their offspring up to 1 year of age.

For analyses of the primary and secondary endpoints, only women treated with basal insulin will be included. However, information on all insulins and other injectable antidiabetic treatment regimens will be collected to facilitate comparison and analysis of outcomes in IDet-treated patients versus, for example, patients treated with an insulin pump.

Any change in basal insulin after the baseline visit will lead to exclusion from the statistical analyses of the primary and secondary endpoints, but not from the study. However, changes in dosage or dose interval, or add-on/removal of bolus insulin, oral antidiabetic drugs and/or glucagon-like peptide-1 (GLP-1) agonists, will not lead to exclusion from the analyses.

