### Determination of sample size

The sample size calculation was derived from the primary endpoint, based on patients with none of the three individual outcomes: major congenital malformations, perinatal death or neonatal death. The probability of this combination of endpoints is not known within the literature. However, based on data from a UK population study [10], which are in line with results from other European countries [1, 2, 4, 11–13], the proportion of pregnancies with any of the above outcomes is estimated at 8.2%: major congenital malformations, 4.5%; perinatal death, 3%; neonatal death, 0.9% (8.2% is computed under the assumption that the individual outcomes are independent). The proportion of pregnancies *without* any of the above outcomes is therefore estimated at 91.8%.

The goal is to be able to detect a difference of 3.5% between the proportions without the combined endpoint in the IDet group compared with the other basal insulin regimens group. Assuming a maximum 1:2 split between the two groups (IDet group: other basal insulin regimens group), a sample size of 1833 pregnancies is needed to have 80% power of achieving significance at a 5% level.

To achieve a total of 1833 pregnancies for the assessment of the primary endpoint, the planned number of patients to be included during the 5 years of the recruitment period is 3075. This number is based on the expectation that ~20% of pregnancies will result in a spontaneous abortion, ~10% will be treated with other antidiabetic injectables or will change basal insulin treatment and ~10% will be lost to follow-up, leaving 60% of pregnancies (i.e., 1833) assessable for the primary endpoint.

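### The stated analysis set keeps spontaneous abortions, which the crude primary analysis would mostly count as event-free, while the sample size treats them as not assessable

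*Protocol article*

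**What the plan says.** All places are in the protocol article, under Methods/design.

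- **Statistical considerations** fixes the analysis set: "The analysis set will consist of all pregnancies among patients who are treated with basal insulin and have not changed basal insulin product", over the four weeks before conception and during pregnancy. The primary endpoint is then analysed in two ways. One is a logistic regression whose covariates include HbA1c at the end of the second trimester. The other is the crude proportion per group, with the absolute difference, a 95% CI and Fisher's exact test.
- **Study endpoints** defines success as pregnancies "which do not result in any of the following events: major congenital malformations, perinatal death or neonatal death". Besides the restriction to basal-insulin users, its one exclusion is: "Any change in basal insulin after the baseline visit will lead to exclusion from the statistical analyses of the primary and secondary endpoints". The same section lists early loss as a secondary endpoint: "Perinatal outcome endpoints include the proportion resulting in fetal macrosomia, LGA, preterm delivery or spontaneous abortion".
- **Table 1** defines spontaneous abortion as "A naturally occurring termination of a pregnancy before 22 completed gestation weeks" and perinatal death as "Death of a foetus/infant at ≥22 completed gestational weeks and <1 completed week after delivery".
- **Determination of sample size** explains the recruitment target: "This number is based on the expectation that ~20% of pregnancies will result in a spontaneous abortion". It takes off about 10% for other injectables or a change of basal insulin and about 10% for loss to follow-up, "leaving 60% of pregnancies (i.e., 1833) assessable for the primary endpoint".

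**The concern.** The Table 1 definitions do not overlap: perinatal death begins at 22 completed weeks, and spontaneous abortion ends before that point. A miscarriage with no detected major malformation therefore meets none of the three event definitions. The analysis set does not exclude it, so it falls on the success side of the crude comparison. The sample-size section treats the same pregnancies as outside the primary assessment. The article thus gives two denominators for one endpoint.

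What is at stake is mainly the meaning of the result. This is a post-authorisation safety study requested by a regulator, and under the analysis-set wording an early loss would improve an insulin's primary safety figure. Treatment is not randomised, so equal early-loss rates cannot be taken for granted. The 8.2% event rate and the 3.5-point target difference would also no longer describe the analysed pregnancies. Finally, the two stated primary analyses would probably rest on different populations.

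**Working it through.** **1. Reproduce the plan's figures.** Inputs from Determination of sample size: malformation 4.5%, perinatal death 3%, neonatal death 0.9%, treated as independent; difference 3.5 points; split 1:2; power 80%; 5% level (two-sided, from Statistical considerations).

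- Composite: 1 − 0.955 × 0.97 × 0.991 = 8.2%, so 91.8% event-free.
- Detemir better by 3.5 points (95.3% against 91.8%): the pooled two-proportion formula gives about 1793 in total. Fisher power at 611/1222 is 80.3%, so 1833 is reproduced.
- Detemir worse by 3.5 points (88.3% against 91.8%): Fisher power at 611/1222 is 65.2%. This is the baseline for any statement about detecting harm.
- 100% − 20% − 10% − 10% = 60%, and 1833/0.60 = 3055. The 60% is reached only by removing the spontaneous abortions.

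**2. Share of early losses if they are kept.**

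- No overlap with the other removals: 20/(20 + 60) = 25%. Total N = 1833/0.75 = 2444.
- Losses spread evenly over the other categories: 20%. Total N = 1833/0.80 = 2291.

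**3. Dilution with equal loss shares.** Multiply each event rate by (1 − share).

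| Loss share | Reference event rate | 3.5-point difference becomes |
|---|---|---|
| 25% | 8.2 × 0.75 = 6.15% | 3.5 × 0.75 = 2.6 points |
| 20% | 8.2 × 0.80 = 6.56% | 3.5 × 0.80 = 2.8 points |

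**4. Power with equal loss shares (25%).** Fisher's exact test, 611/1222 with losses excluded and 815/1629 with losses included.

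| True rates after early loss, detemir vs other | Excluded | Included |
|---|---|---|
| Benefit, 4.7% vs 8.2% | 80.3% | 79.4% |
| Harm, 11.7% vs 8.2% | 65.2% | 64.0% |

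The number of events is the same and only event-free pregnancies are added, so power barely moves.

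**5. Unequal loss shares.** The shares are assumptions; the document gives none by group. With the same 8.2% risk in both groups after early loss, the spurious difference is 8.2 × (difference in shares):

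- 25% against 20%: 8.2 × 0.05 = 0.4 points in favour of the group with more losses.
- 30% against 20%: 8.2 × 0.10 = 0.8 points.

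Now take 30% for detemir and 20% for the others, with a true harm of 11.7% against 8.2%:

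- Included (815/1629): 11.7 × 0.70 = 8.2% against 8.2 × 0.80 = 6.6%. Fisher power is about 30%.
- Excluded from the same data (815 × 0.70 ≈ 570 and 1629 × 0.80 ≈ 1303): 11.7% against 8.2%. Fisher power is about 64%.

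**6. The adjusted model.** A pregnancy lost before 22 completed weeks will in general have no HbA1c value for the end of the second trimester. Unless values are imputed, the logistic regression drops it, while the crude comparison keeps it.

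**The case against.** The strongest reply is that the sample-size section already says who is assessable for the primary endpoint. The broad analysis set serves every endpoint, including spontaneous abortion, so it has to contain these pregnancies. A wide set with an assessable subset for the primary endpoint is a reasonable joint reading, and probably the intended one. The analysis-set wording does not exclude women lost to follow-up either, yet nobody would score them as successes. This stands as a reading of intent. It does not remove the conflict: the exclusion appears only in a recruitment calculation, while the sentence that fixes the analysis set names no such subset. A miscarriage also differs from a loss to follow-up in that its outcome is known.

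Three stronger readings are tempting, and the documents do not support them:

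- *Every miscarriage is scored a success.* A loss with a detected major malformation is an event, and the logistic model would probably drop most early losses. The problem lies mainly in the crude proportions, their difference and Fisher's test.
- *The study loses its power, from 80% to 30%.* With equal loss rates almost nothing is lost. The 30% figure needs an assumed 30% against 20% split, and its proper baseline is about 64%.
- *A difference in miscarriage would be hidden.* Spontaneous abortion is a secondary endpoint, and Statistical considerations applies similar analyses to the other proportions.

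It is also fair to say that excluding early losses conditions on something that happens after exposure, so exclusion does not by itself guarantee an unbiased comparison.

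**Conclusion.** The point holds as a conflict between stated rules: the analysis set and endpoint definition on one side, the sample-size section on the other. It is not a detail left to an analysis plan, because the article does state an analysis set.

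Read as written, the crude primary analysis would contain about 20–25% early losses, nearly all counted as event-free apart from those with a detected major malformation. The consequence is a diluted estimand and a bias toward whichever group loses more pregnancies early. The dilution figures rest on the plan's own 20%, 60%, 8.2% and 3.5 points. The bias figures of 0.4 and 0.8 points, and the fall in power for harm from about 64% to about 30%, rest on assumed group-specific loss rates that the document neither gives nor contradicts. That the two primary analyses would use different populations assumes no imputation of the missing HbA1c value.

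**What to change.** Amend the analysis-set text in Statistical considerations to say that, for the primary endpoint:

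- pregnancies ending before 22 completed weeks without a confirmed major malformation are excluded from numerator and denominator, in line with the sample-size section;
- a loss with a confirmed major malformation counts as an event.

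Keep the full set for the spontaneous-abortion secondary endpoint, and report the primary result beside that comparison, so that a reader can judge whether unequal early loss could have influenced it. A sensitivity analysis counting any loss as an event is optional.

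The cost is a sentence or two. The 1833 target stands, and no new data are needed.

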### Study organisation

The study is being conducted across approximately 53 study sites in 14 countries. The anticipated numbers of patients per country are as follows: Croatia, 355; Denmark, 620; Finland, 100; France, 150; Germany, 135; Israel, 350; Italy, 130; Netherlands, 100; Poland, 200; Romania, 60; Spain, 375; and UK, 300. Additional countries and study sites might be included during the study period. Sites have relatively similar standard routine procedures with regard to the treatment of women with diabetes during pregnancy and have a relatively high prescription rate of IDet. The projected study timeline is given in Fig. 2.

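### The primary logistic model pools type 1 and type 2 diabetes but leaves diabetes type, known at entry, off its adjustment list

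*Protocol article*

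**What the plan says.** In the Protocol article, Statistical considerations, the primary endpoint is analysed with "a logistic regression model that will include treatment group, study site, race, hypertension". The factor list continues with major hypoglycaemia and ends with "folic acid intake and use of GLP-1 agonists during pregnancy as factors". The covariates are HbA1c at three times in pregnancy and then "age and body mass index at baseline, duration of diabetes, blood pressure and previous perinatal complications will be included as covariates". Diabetes type is in neither list. Its only use in the analysis is as an example of a descriptive breakdown: "such as the primary endpoint split out according to diabetes type, insulin analogue or use of an insulin pump".

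Type is available for every woman. Table 2 makes it an entry condition: "Type 1 diabetes or type 2 diabetes, diagnosed prior to conception". Methods/design states that treatment follows current practice and is not assigned by the protocol. The infant endpoints at 1 year take over the primary model's factors and covariates, and similar analyses are planned for the other endpoints that are proportions.

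On sites, Study organisation says: "The study is being conducted across approximately 53 study sites in 14 countries". It adds that more may join.

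**The concern.** In a non-randomised comparison, the regression is the analysis that has to deal with differences between women who receive insulin detemir and women who receive another basal insulin. The Fisher's exact test and the absolute difference reported beside it are unadjusted. Diabetes type could plausibly bear on both the choice of insulin and the outcome. The article treats the two types differently: its Background says that all women with type 1 but only many with type 2 will need insulin, and the one cited randomised trial of insulin detemir in pregnancy enrolled type 1 only.

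If the groups differ in type and the types differ in risk, part of that difference is attributed to the insulin. The listed covariates capture some of it indirectly, but the variable itself is on file and costs nothing to use. Because the list is reused, the gap carries over to the infant and other binary endpoints.

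A lesser question is how study site enters. About 53 levels are many for the expected number of events.

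**Working it through.** **The plan's own figures.** Determination of sample size gives major malformation 4.5%, perinatal death 3% and neonatal death 0.9%.
- Composite: 1 − 0.955 × 0.970 × 0.991 = 0.082, as stated.
- Sample size: 4.7% (insulin detemir) against 8.2% (other), two-sided 5%, 80% power, 1:2 split, pooled variance, gives 598 + 1196 = 1794, within 3% of the stated 1833. Power at 611:1222 is 80.9%.
- Expected events: 1833 × 0.082 = 150 with 8.2% in both groups. With 4.7% on insulin detemir: 611 × 0.047 + 1222 × 0.082 = 129. With 11.7%: 611 × 0.117 + 1222 × 0.082 = 172.

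**What omitting type could do.** The article gives neither the type split by insulin group nor a type 1 versus type 2 risk gap, so both inputs are assumptions.
- Crude shift = (difference in type share) × (risk gap between types).
- Assumed shares of type 1: 85% against 60%, a difference of 0.25. Assumed gap: 0 to 4 points.
- Result: 0.25 × 0 = 0 to 0.25 × 4 = 1.0 point, against a target of 3.5 points.
- The result is only as good as its inputs. With the same 0.25 and a type odds ratio of 2.0 around 8.2%, the higher risk is 15.2%, the gap 7.0 points and the shift 1.7 points. With no gap it is 0.

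These are shifts before any adjustment. What remains after duration, age, BMI, HbA1c and blood pressure cannot be computed from the article.

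**Site, if fitted as a fixed factor.**
- Site parameters: 53 − 1 = 52.
- Other parameters, at least: 6 factor terms (treatment, race counted as one, hypertension, major hypoglycaemia, folic acid, GLP-1 agonist) + 8 covariate terms = 14.
- Total: at least 66. Events per parameter: 150 / 66 = 2.3 (129 / 66 = 2.0; 172 / 66 = 2.6).
- Sites with no event give no information on treatment in such a model. With equal sites (about 35 pregnancies each), about 3 to 5 would have none. With uneven sizes (assumed), about 12 to 14 would, holding about 114 to 142 pregnancies, or 6% to 8% of 1833.

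**Does that sparseness hurt the treatment estimate?** Three simulations with 53 uneven sites, all on assumed site structure:

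| Setting | With site | Comparator |
|---|---|---|
| 300 runs, prescribing unrelated to site, true log-OR −0.59 | mean −0.62, SD 0.22, power 81.7% | no site: mean −0.61, SD 0.21, power 81.3% |
| Same, null | rejects 6.3% | no site: 6.7% |
| 350 runs, OR 0.552 | power 74.6% | country: 76.6% |
| 350 runs, OR 1.48 | power 57.4% | country: 64.3% |
| 350 runs, null | at or below 5% | country: at or below 5% |
| Third simulation, OR 1.48, prescribing unrelated to site | power 66.5% | country: 66.9% |
| Third, prescribing varies by site | power 60% | country: 66% |
| Third, prescribing correlated with site risk (0.5), true log-OR 0.394 | mean 0.406 | country: mean 0.483 |
| Same, null | rejects 4.8% | country: 8.4% |

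The third simulation had about 620 to 645 usable runs of 700 per scenario; non-converged fits were dropped.

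**The case against.** **On diabetes type.** The strongest reply is that the proxies are many. Besides duration, age and BMI, the model holds three HbA1c values, hypertension, blood pressure and GLP-1 agonist use, and together these may separate the two types fairly well. Nothing in the article shows that type differs between the insulin groups, or that risk differs between types; the rates quoted in the Background are for type 1. A reader might infer from the 0 to 1.0 point figure that the primary estimate is known to be biased by about that much. The documents do not support this: the figure is crude, rests on assumed inputs and includes zero. What stands is that proxies are a weaker choice than the recorded variable, and the article gives no reason for preferring them.

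It can also be said that the sample size fits the unadjusted two-proportion comparison, which the covariate list does not touch. That is true. It limits the point to the adjusted analysis, but that is the analysis meant to handle confounding.

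**On site.** A reader might infer from roughly 2 events per parameter that the odds ratio is unstable and that country should replace site. The simulations do not bear this out. The SD of the treatment coefficient barely moves, null rejection is not raised by the site term, and the larger power losses are confined to some scenarios. Where prescribing and risk vary together by site, dropping to country biases the estimate and raises false rejections. Site is a plausible confounder here, so adjusting for it is defensible. The article also does not say outright that site is fixed; calling it a factor makes that the natural reading, and the handling of sparse sites may be settled in the analysis plan.

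**Conclusion.** The omission is real. The adjustment list is set out term by term, diabetes type is not on it, and type is known for every woman and singled out as a split of possible clinical importance. In a non-randomised study, the adjusted comparison then relies on proxies for a variable that could have been entered directly, and the same holds wherever the list is reused.

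The size of the residual confounding is unknown. Under an assumed 25-point imbalance and a 0 to 4 point risk gap, the crude shift is 0 to 1.0 points against the 3.5-point target, and less after the proxies. The case for change rests on the low cost of the remedy, not on a demonstrated bias.

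The site arithmetic is right if site is a fixed factor: about 52 parameters, about 150 events, and no contribution from event-free sites. The simulated harm is mild, so this is a note and not a reason to remove site adjustment.

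**What to change.** Add diabetes type (type 1 or type 2) as a factor in the primary logistic model, in the 1-year infant models that take over its list, and in the similar analyses of the other proportions. Keep the descriptive split by type.

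This costs one degree of freedom and no new data. The parameter count under a fixed site factor goes from at least 66 to at least 67, still about 2.2 events each (150 / 67). The Fisher's exact test and the crude difference are unchanged.

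Keep study site in the model and do not replace it by country. A model with a random intercept for site may be added as an optional sensitivity analysis: it retains site adjustment and lets event-free sites contribute, but it assumes that site effects are unrelated to prescribing, so it should sit beside the main model and not displace it.

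### The primary logistic model adjusts for in-pregnancy HbA1c and major hypoglycaemia, which follow exposure and are also secondary endpoints, so it does not estimate the total effect of detemir

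*Protocol article*

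**What the plan says.** All references are to the protocol article; the statistical analysis plan is not shown.

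- **Exposure.** Under Statistical considerations, the analysis set is pregnancies in women on basal insulin who "have not changed basal insulin product for 4 weeks prior to conception and during pregnancy".
- **Model factors.** The primary logistic model contains treatment group, study site, race and hypertension, followed by "major hypoglycaemic events during pregnancy, folic acid intake and use of GLP-1 agonists during pregnancy as factors".
- **Model covariates.** HbA1c enters three times, at "the start of pregnancy, the end of the first trimester and the end of the second trimester, age and body mass index at baseline". Diabetes duration, blood pressure and previous perinatal complications are also listed.
- **Same variables as endpoints.** Under Study endpoints: "Maternal endpoints include the incidence of major hypoglycaemia during pregnancy, the proportion of pregnancies complicated by pre-eclampsia and metabolic control", the last measured as HbA1c. These are compared between detemir and the other basal insulins.
- **Event window.** Table 1 defines perinatal death as "Death of a foetus/infant at ≥22 completed gestational weeks and <1 completed week after delivery".
- **Second analysis.** Group proportions are also computed and the "absolute difference between these proportions calculated, along with the 95% CI and the" p-value from Fisher's exact test. This uses no covariates.

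**The concern.** The primary objective compares pregnancy outcome between detemir and other basal insulins. That is a question about the total effect of the insulin, whatever its route. Because the product is fixed before conception, HbA1c three or six months later cannot have influenced which insulin the woman was on. It can, however, be a result of that insulin, and the plan itself treats it, and major hypoglycaemia, as results. The Background section reports that HbA1c before and during pregnancy is associated with perinatal death and malformation, so it is a plausible step between insulin and primary outcome.

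Conditioning on such a step takes out the part of the effect that runs through it. If the step also shares unmeasured causes with the outcome, conditioning adds bias of unknown sign. In a safety study requested by a regulator, harm or benefit acting through glycaemia or hypoglycaemia could be obscured in the only primary comparison that controls for confounding.

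A second problem is structural. HbA1c at the end of the second trimester cannot exist for a pregnancy that ended before then, yet deaths count as primary events from 22 completed weeks.

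**Working it through.** **1. The plan's own figures** (Determination of sample size)

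- Combined event rate: 1 − (0.955 × 0.970 × 0.991) = 8.20%. This matches the stated 8.2%.
- Sample size for 95.3% versus 91.8% event-free, 1:2 split, two-sided 5%, 80% power. With p̄ = (0.953 + 2 × 0.918)/3 = 0.9297, n in the smaller group = [1.960 × √(1.5 × p̄(1 − p̄)) + 0.8416 × √(0.953 × 0.047 + 0.918 × 0.082/2)]² / 0.035² = 598. The total is 598 + 1196 = 1794, which is 2.1% below the stated 1833.
- This is an unadjusted two-proportion calculation, so the covariate list does not alter the planned number.

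**2. Timing and role of each questioned variable**

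| Variable in model | Relation to exposure | Also an endpoint? |
|---|---|---|
| HbA1c, end of first and second trimester | after | yes (metabolic control) |
| Major hypoglycaemia during pregnancy | after | yes |
| GLP-1 agonist use during pregnancy | after; a permitted co-treatment change | no |
| Folic acid, hypertension, blood pressure | timing not stated | no |
| HbA1c, start of pregnancy | strictly after the four-week run-in, but close to it | no separate role |

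**3. What conditioning can do to the odds ratio** (illustrative; no input comes from the documents)

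Let c be the direct log odds ratio, a the shift in the mediator due to insulin (in SD), and b the log odds ratio of the outcome per SD of mediator. The total is roughly c + ab, and the adjusted model returns c. Take c = −0.4 (OR 0.67).

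- a = −0.1, b = 0.4: share removed = 0.04/0.44 = 9% (simulation 8%).
- a = −0.3, b = 0.6: share removed = 0.18/0.58 = 31% (simulation 30%).
- a = 0: nothing removed (simulation: essentially none).
- a = +0.3, b = 0.4: total = −0.28 (OR 0.76), adjusted = −0.4 (OR 0.67). Here adjustment exaggerates the benefit, so the error can go either way.

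**4. Events that a complete-case fit could lose**

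- Expected primary events: 1833 × 0.082 = 150. Expected perinatal deaths: 1833 × 0.03 = 55.
- Let s be the share of perinatal deaths in pregnancies ending between 22 completed weeks and the end of the second trimester. The documents give no such share, so 10% to 50% is assumed.
- Events lost = 55 × s: 5.5 at s = 10%, 27.5 at s = 50%.
- Share of all primary events: 5.5/150 = 3.7% to 27.5/150 = 18.3%.
- Event rate left in the model: (0.082 − 0.03s)/(1 − 0.03s), which is 7.9% to 6.8% instead of 8.2%.

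**The case against.** The best defence has four parts.

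1. **Little may run through these variables.** The Background section reports similar HbA1c and hypoglycaemia rates for detemir and NPH in the earlier randomised trial, and comparable glycaemic control for detemir and glargine in a retrospective series. The Discussion calls late-pregnancy HbA1c non-inferior. This stands as a limit on size. It does not show that mediation is absent: the trial covered type 1 diabetes and NPH only, while this cohort includes type 2 diabetes and every other basal insulin. A reader might infer that a large, known fraction of the detemir effect is removed, with a matching loss of power. The documents supply no mediated share, so that reading is not supported.

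2. **An unadjusted analysis is planned too.** This also stands: the difference in proportions and Fisher's test use no covariates and lose no pregnancy to a missing HbA1c. But treatment is not assigned by the protocol, so that analysis cannot replace a sound adjusted one.

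3. **No loss of events is stated.** Correct. A reader might conclude that early deaths are dropped from the analysis. The article gives no rule for missing covariates, and one may stand in the analysis plan. Any loss needs a complete-case fit, touches only the logistic model, and is confined to the window from 22 completed weeks to the end of the second trimester. Even so, the value is not merely unrecorded but cannot exist, which a general missing-data rule would not easily repair.

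4. **GLP-1 use is a co-treatment.** Also correct. Nothing in the article shows it to be a pathway of basal insulin. The point against it is only that it is recorded after exposure began.

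**Conclusion.** The concern holds as a fault in a model that the article itself specifies. Adjusting for later HbA1c and major hypoglycaemia means that the adjusted odds ratio does not answer the stated objective, and the only confounding-controlled primary estimate is the one affected. That conclusion rests on the article's own timing and endpoint list and needs no assumption.

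The size does rest on assumptions. The distortion may be near zero if insulin hardly moves these variables; under the illustrative inputs it is 8% to 30% of the log odds ratio, and its sign is not fixed. The possible loss of about 5 to 27 of about 150 events depends on complete-case fitting and on the assumed 10% to 50% share. The planned sample size is unaffected.

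**What to change.** Limit the main adjusted model to variables fixed at or before baseline:

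- Keep study site (about 53 sites are planned), race, age, body mass index, diabetes duration and previous perinatal complications.
- Keep HbA1c at the start of pregnancy, and say that it serves as a proxy for pre-pregnancy control, since exposure had strictly begun by then.
- Use baseline values of hypertension, blood pressure, folic acid intake and GLP-1 agonist use where recorded. The article does not state their timing, or whether GLP-1 use at baseline is captured separately, so this must be checked against the data collection forms.
- Move end-of-first- and end-of-second-trimester HbA1c, major hypoglycaemia and in-pregnancy GLP-1 use to a supplementary or mediation analysis labelled as such. State there how pregnancies that ended before an HbA1c time point are handled.

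The currently listed model can survive as that supplementary analysis. The cost is one additional model, and the change should be made before outcome data are analysed.
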